### Patient allocation and blinding

Each patient is allocated to either arthroplasty or simple discectomy by randomly drawing an unmarked opaque sealed envelope from a non-sequential stack. Randomization is performed in a 1:1 ratio without a fixed block size. The patient is informed about the result of the randomisation at the first radiological examination moment, up to two days before surgery. The surgeon and other caregivers are not blinded. Assessment of the radiological data is not blinded, since absence or presence of a prosthesis is clearly visible. The clinical outcome data are collected by a blinded caregiver.

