Prevention of ASDis is based on the premise that mobile disc prostheses preserve cervical spine motion in a physiological way. Motion of the cervical spine is commonly measured by means of flexion-extension radiographs, which give information about the segmental range of motion (sROM). It suffers from a high intra- and inter-individual variability, severely limiting its use as a tool for diagnosis and follow-up in the individual patient. The sequence in which motion segments contribute to the movement to maximum extension or flexion in the entire cervical spine has been reported to be a more consistent parameter in healthy controls [13-15]. Therefore, a randomized controlled study to investigate the influence of implanting a mobile disc prosthesis on motion in the cervical spine was designed, using analysis of the sequence of segmental contributions.

Primary objective of the study is to ascertain whether a mobile cervical disc prosthesis restores/preserves the sequence of segmental contributions that is present in healthy controls, in contrast to patients undergoing simple discectomy. Secondary goal is to evaluate the clinical results of CDA with the prosthesis used, compared to simple discectomy, to determine if results are comparable to reported results for this type of surgery.

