### Radiological outcome measures

Radiological outcome measures are evaluated pre-surgery (0–2 days), and at three and twelve months post-surgery. Radiological outcome measures are:Absence or presence of normal sequence of segmental contributions to cervical spine movement, analysed through fluoroscopic flexion-extension recording (FFER). The method of data acquisition and analysis is described below.Segmental range of motion (sROM) of the target level is measured.The presence of fusion is defined by cortical bridging and/or sROM less than < 2°.

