### Radiological data processing

The authors have developed custom software that uses image recognition algorithms to track the skull and cervical vertebrae during flexion and extension throughout these series of frames [16]. The software follows bony structures within user-defined template areas (splines) throughout all frames, using a best-fit principle to match normalized gradient field images. To define these template areas the user of the software draws polygons around all vertebrae and part of the skull on the median frame of the recording (Additional file 2: Figure S1). After the software has completed tracking these structures they can be manually evaluated, and corrections can be made if necessary.

The rotational data between frames for each bony structure enables the user to calculate sROMs, but also sagittal rotation within a motion segment through time. The sequence of various segmental contributions to movement of the entire cervical spine can therefore be established (Additional file 3: Figure S2). The sequence of segmental contributions is evaluated during full ‘bending’ extension-to-flexion, and vice versa. It is compared to ten healthy controls, and a historical control group [13-15].

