As in almost all surgical studies, caregivers and X-ray analyses cannot be blinded, and patients report their own outcomes, therewith invoking risk of bias. This is a common weakness in this type of study, as blinding patients in these types of device studies is often regarded as not ethically appropriate, and most of the clinical outcomes are patient-reported outcomes [10]. As a result, many of the outcomes may suffer from bias, although the differences that have been reported so far were usually small [10]. The radiological outcome cannot be blinded completely since the prosthesis is clearly visible in the FFER, and although the motion analysis is performed by image recognition software, these analyses are checked manually to avoid errors. The clinical outcome data are collected by a blinded caregiver; since the patient is not blinded the possibility of the caregiver receiving information about the surgery is therefore present. Sample size is small in this study. However, given the large expected difference in the amount of fusion between the groups, and the consistent findings when analysing sequence of segmental contributions, the authors expect to be able to draw conclusions about the primary outcome. For the secondary outcomes the sample size will be too small. However, the authors’ haven previously shown that clinically relevant differences are not to be expected, and only aim to see if results are in line with those described in literature [10].

The study is industry sponsored, as are most of the RCTs on this subject [10]. This also can lead to bias. The influence of a conflict of interest on outcomes in trials investigating CDA has recently been investigated, which led to the conclusion that while there was no influence on quality of life outcomes, it was associated with lower reported complication rates [12]. In the current study the sponsor has no influence on planning or conducting the study, no influence on data acquisition or analysis, or any aspect of the publication process.

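### Prosthesis visibility explains unblinded tracking of the recordings, but not unblinded classification of the primary outcome, which is derived from rotation-time data

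*Protocol article*

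**What the plan says.** - **Primary outcome.** Background: "Primary objective of the study is to ascertain whether a mobile cervical disc prosthesis restores/preserves the sequence of segmental contributions". Radiological outcome measures and Statistical methods make this a yes/no outcome, compared by χ² or, with small cells, Fisher's exact test at P < 0.05.
- **Blinding.** Patient allocation and blinding: "Assessment of the radiological data is not blinded, since absence or presence of a prosthesis is clearly visible". The Discussion repeats the reason, but says only that complete blinding of the radiological outcome is not possible.
- **Image stage.** Radiological data processing: a user outlines the vertebrae and part of the skull on one frame and the software tracks them. Afterwards "they can be manually evaluated, and corrections can be made if necessary". The Discussion adds that "these analyses are checked manually to avoid errors".
- **Numerical stage.** Same section: "The rotational data between frames for each bony structure enables the user to calculate sROMs, but also sagittal rotation within a motion segment through time". It continues: "The sequence of various segmental contributions to movement of the entire cervical spine can therefore be established". The result is compared with ten healthy controls and a historical control group.
- **Sample size.** Ten evaluable patients per arm, twelve randomised per arm.

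**The concern.** The article gives one reason for leaving the whole radiological assessment open: the implant shows on fluoroscopy. By its own account, the primary outcome is not read from fluoroscopic frames. It is derived from the rotation of each segment over time, after tracking. A rotation-time curve shows no implant, so the reason does not reach the classification step.

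At stake is the primary comparison in a trial of 24 randomised patients. If whoever classifies the sequence knows the arm and has any discretion, a few borderline calls could lean one way. The clinical outcomes are collected by a blinded caregiver, so on paper the primary outcome has less protection at the assessor level than the secondary ones.

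**Working it through.** The plan states no figure on this point, so there is none to reproduce. The check traces the outcome step by step and then illustrates sensitivity with assumed inputs.

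**1. Where the stated reason applies**

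| Step (Radiological data processing) | Needs the images? | Does visibility of the prosthesis explain lack of blinding? |
|---|---|---|
| Drawing templates on the median frame | Yes | Yes |
| Software tracking, manual evaluation and correction | Yes | Yes |
| Computing segmental rotation over time | No | No |
| Establishing the sequence; normal or not | No, it follows from the rotation data | No |

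The figure showing the curves is in an additional file that is not available. That the curves contain no image is inferred from the text.

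**2. How far a few calls can move the test (counts are assumed)**

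With ten per arm and eight normal sequences in total, the probability of a in one arm and 8 − a in the other is C(10,a)·C(10,8−a)/C(20,8), with C(20,8) = 125,970.

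- 6/10 vs 2/10: tail = (9,450 + 1,200 + 45)/125,970 = 0.0849. Two-sided p = 2 × 0.0849 = 0.170.
- 7/10 vs 1/10: tail = (1,200 + 45)/125,970 = 0.0099. Two-sided p = 2 × 0.0099 = 0.020.
- 5/10 vs 3/10: two-sided p = 1 − 44,100/125,970 = 0.65. One call moved in each arm gives 6/10 vs 2/10, still p = 0.17.

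With twelve per arm, C(24,8) = 735,471:

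- 6/12 vs 2/12: 2 × (60,984 + 9,504 + 495)/735,471 = 0.193.
- 7/12 vs 1/12: 2 × (9,504 + 495)/735,471 = 0.027.

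One call in each arm can cross 0.05 from one starting point and not from another.

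**3. False-positive rate under differential scoring (rates and shares are assumed)**

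Let both arms have the same true proportion p of normal sequences, and let a share f of abnormal arthroplasty cases be called normal. The observed arthroplasty proportion is then q = p + f(1 − p); for example, p = 0.20 and f = 0.40 give q = 0.20 + 0.40 × 0.80 = 0.52. The rejection rate sums the binomial probabilities of all count pairs with two-sided Fisher p < 0.05.

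| Patients per arm | p | f = 0 | f = 20% | f = 40% |
|---|---|---|---|---|
| 12 | 20% | 1.2% | 6.2% | 24.2% |
| 12 | 30% | 1.7% | 5.3% | 18.2% |
| 12 | 50% | 2.3% | 3.9% | 9.4% |
| 10 | 20% | 0.8% | 4.0% | 15.2% |
| 10 | 30% | 1.2% | 3.2% | 10.6% |
| 10 | 50% | 1.3% | 2.2% | 5.5% |

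At f = 20% the rate stays near or below 5%, because Fisher's test is conservative at this size. At f = 40% it exceeds 5% in every row. Nothing in the article indicates what f would be, or how it would divide between tracking and classification.

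**The case against.** The strongest reply is that the operator-dependent steps the article describes are template drawing and tracking correction. Both need the images, and coding the curves reaches neither. If the sequence then follows from the rotation data by a fixed rule, blinding the classification changes little. This stands as a limit on the benefit. It does not supply a reason for leaving classification open, and locking the tracking first would still help.

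Second, coded curves may partly reveal the arm. The article expects a 40% difference in fusion, cites fusion of up to 80% after simple discectomy, and notes that a fused segment leaves a missing peak. This also stands, but the article allows for fusion in either arm, so a missing peak is a hint and not an identification.

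Third, the limitation is disclosed. That is true, but the disclosure rules out only complete blinding and does not address the separable step.

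A reader might go further and infer that the call is subjective, that whoever corrects the tracking sees the resulting sequence, or that most of the bias is avoidable. The article supports none of these. It does not say how the call is made, and it describes manual correction before it describes the rotation data and the sequence. Industry sponsorship adds little here, since the Discussion states that the sponsor has no influence on data acquisition or analysis.

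**Conclusion.** The point holds in a limited form. The reason given for unblinded radiological assessment covers template drawing and tracking correction, but not classification of the sequence, which is the primary outcome. Partial blinding of that step is feasible on the article's own description and is not described.

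The size of the bias avoided is unknown, because the article does not say whether the call is made by eye or by rule. The Fisher example might be taken to mean that two calls out of 20 decide the trial. It does not show that: the counts are assumed and start just short of significance, and the same shift from 5/10 vs 3/10 changes nothing of consequence. It shows only that a few calls can matter with ten to twelve patients per arm. The conclusion rests on the inference that the rotation-time curves carry no image information. This is an inexpensive improvement to the plan, not a flaw that invalidates the design.

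**What to change.** 1. Complete the tracking and all manual corrections for each recording, and lock it before any sequence is computed.
2. Export only the segmental rotation-time data under random codes, with arms and visits shuffled together and mixed with the curves of the ten healthy controls. This assumes that the controls' data can be exported in the same form.
3. Classify each coded curve as normal or abnormal, preferably by a fixed rule in the software. If a person makes the call, that person works from the codes alone. A reader who also tracked the recordings may recognise some of them, which is a further reason to prefer a rule.
4. Break the code only after all calls are locked.
5. Report the number of manual corrections by arm, and state in the blinding section which steps are blinded and which are not.

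The cost is a short export and coding script and a written procedure, with no extra reader, imaging or patients. Two weaknesses remain and should be stated: tracking corrections are still unblinded, and a missing peak may hint at the arm.

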### Interventions

All patients are operated in the same centre by a single experienced spine surgeon. The prosthesis used is the Activ-C (B. Braun Aesculap, Germany).Surgery is performed under general anaesthesia, with the patient in a supine position and the neck in a neutral position to slight extension. Antibiotic prophylaxis is given at induction of anaesthesia. The location of the incision is verified using fluoroscopy. In case of poor visibility of the target level, the shoulders are retracted by elastic tape. A transverse incision is made on the right side of the neck. The anterior aspect of the cervical spine is approached medially to the carotid sheath. The level is verified during surgery using fluoroscopy. The vertebral bodies are then distracted using two distraction pins and a Caspar spreader. Using a microscope, a standard discectomy is performed. The posterior longitudinal ligament is opened to reveal any sequesters. Decompression is verified by probing of the neuroforamen. In the simple discectomy group haemostasis is checked, a low-vacuum drain is placed and the wound is closed in two layers.

In the arthroplasty group the correct prosthesis size is chosen using a fitting-prosthesis, the position is controlled by lateral en anterior–posterior fluoroscopy, taking care to place it in the midline. Subsequently, the caudal endplate is prepared for the keel of the prosthesis and the prosthesis is placed. The definite position is checked using fluoroscopy in 2 directions. The wound is rinsed to clear any drilling material, haemostasis is checked, a low-vacuum drain is placed and the wound is closed in two layers.

### Post-surgical care

Antibiotic prophylaxis is continued for 24 hours in the arthroplasty group. Cervical spine X-rays are acquired the day after surgery and the wound drain is removed. Patients in both groups are encouraged to mobilise, and resume home activities and work as soon as possible. A collar is not prescribed and patients are not routinely referred to a physical therapist. Patients in the arthroplasty group are prescribed indomethacin 50 mg three times a day for a period of three weeks to prevent periprosthetic calcifications, unless they have a history of gastric or intestinal complaints, or previous adverse reactions to non-steroidal anti-inflammatory drugs (NSAIDs). Patients in the simple discectomy group are allowed to use NSAIDs.

### Radiological outcome measures

Radiological outcome measures are evaluated pre-surgery (0–2 days), and at three and twelve months post-surgery. Radiological outcome measures are:Absence or presence of normal sequence of segmental contributions to cervical spine movement, analysed through fluoroscopic flexion-extension recording (FFER). The method of data acquisition and analysis is described below.Segmental range of motion (sROM) of the target level is measured.The presence of fusion is defined by cortical bridging and/or sROM less than < 2°.

### Radiological data acquisition

Fluoroscopic recordings are made with a digital X-ray detector (Toshiba Infinix VC-i, Toshiba Medical Systems Corporation, Japan), capturing frames of 1024 × 1024 pixels, at 10 frames per second. The recordings are stored without compression. To acquire the FFER, the subject is placed on a stool, with his shoulders perpendicular to the digital x-ray receptor plate. The shoulder nearest to it is placed directly against it. The subject is asked to move the head in maximal extension without moving the upper part of his body. As soon as the recording is started, the subject is instructed to move the head in the sagittal plane from maximal extension to maximal flexion, without moving the upper part of the body. The subject is then allowed to relax for a moment, and then the movement from maximal flexion to maximal extension is recorded. The subject is asked to perform each movement in about five to ten seconds. It is important that the subject’s shoulders are kept as low as possible during fluoroscopy to ensure that all the cervical vertebrae are visible.

### Radiological data processing

The authors have developed custom software that uses image recognition algorithms to track the skull and cervical vertebrae during flexion and extension throughout these series of frames [16]. The software follows bony structures within user-defined template areas (splines) throughout all frames, using a best-fit principle to match normalized gradient field images. To define these template areas the user of the software draws polygons around all vertebrae and part of the skull on the median frame of the recording (Additional file 2: Figure S1). After the software has completed tracking these structures they can be manually evaluated, and corrections can be made if necessary.

The rotational data between frames for each bony structure enables the user to calculate sROMs, but also sagittal rotation within a motion segment through time. The sequence of various segmental contributions to movement of the entire cervical spine can therefore be established (Additional file 3: Figure S2). The sequence of segmental contributions is evaluated during full ‘bending’ extension-to-flexion, and vice versa. It is compared to ten healthy controls, and a historical control group [13-15].

### Clinical outcome measures

At the same three time points at which the radiological analysis takes place the subject will be neurologically examined by an independent physician or physician assistant who is blinded to the treatment group. Muscle strength in myotomes C5-Th1 according to the Medical Research Council (MRC) Scale for Muscle Strength, sensory deficits in dermatomes C5-Th1, and deep tendon reflexes, are determined. Cervical spine motion is also estimated (flexion, extension, rotation, and lateral bending, estimated in degrees relative to the neutral position, i.e. the ears are aligned directly over the shoulders). Adverse events (such as infection and re-operation) are registered, and the patients are asked to fill in the following questionnaires:Visual analogue scale for pain radiating to the arm (VAS-arm), on a 100 mm scale, ranging from 0 (no pain at all) to 100 (worst pain imaginable).Visual analogue scale for neck pain (VAS-neck), on a 100 mm scale, ranging from 0 (no pain at all) to 100 (worst pain imaginable).Neck disability index (NDI), a 10-item questionnaire with a maximum score of 50 points (0 points being no perceived disability, and 50 points the maximum amount of disability), to assess perceived disability in work related, and non-work related activities due to neck complaints.Short-form 36 (SF36), a survey to assess general health, by using 36 questions to score 8 sections; physical functioning, social functioning, bodily pain, general health, vitality, mental health, and problems with daily activities due to either physical or emotional complaints.

At the two postoperative time points (three and twelve months) one additional outcome is measured:Odom’s outcome scale, a four-level outcome scale rating patients’ outcome from poor to excellent depending on the level of resolution, improvement, or persistence of pre-operative symptoms.

### Statistical methods

Dichotomous outcome measures (presence of normal sequence of segmental contributions, presence of fusion), and ordinal outcome measures (Odom’s outcome scale) will be analysed using a χ2 analysis. Statistical significance will be defined as P < 0.05 in the χ2 analysis. When the requirements of the χ2 analysis are not met (i.e. less than 5 samples per field) Fisher's exact test will be used. Continuous outcome measures (NDI, VAS, SF36, sROM) will be analysed using an independent samples t-Test, after testing for normality. Statistical significance will be defined as P < 0.05 in the t-Test. If normality is not met, a Mann–Whitney *U* test will be used. All data will be analysed according to the ‘intent-to-treat’ principle, additionally a sensitivity analysis will be performed, based on presence or absence of fusion.

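### Odom's four-grade ordinal scale is compared with a chi-square or Fisher test that ignores the order of the grades; a rank test fits better, though the consequence for this secondary outcome is minor.

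*Protocol article*

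**What the plan says.** In the protocol article, Clinical outcome measures introduces "Odom’s outcome scale, a four-level outcome scale rating patients’ outcome from poor to excellent". It is collected at three and twelve months.

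Statistical methods recognises the data type but puts the scale in the same sentence as the dichotomous outcomes: "ordinal outcome measures (Odom’s outcome scale) will be analysed using a χ2 analysis". A threshold and a fallback follow: "Statistical significance will be defined as P < 0.05 in the χ2 analysis", and "When the requirements of the χ2 analysis are not met (i.e. less than 5 samples per field) Fisher's exact test will be used".

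A rank test does appear in that section, but only as the fallback for the continuous measures (NDI, VAS, SF36, sROM): "If normality is not met, a Mann–Whitney" U test replaces the t-test. No trend version of chi-square, ordinal model or dichotomisation is named for Odom's scale.

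**The concern.** The plan names the scale as ordinal and then assigns it a test for unordered categories. On a 2×4 table, chi-square and Fisher's exact test ask whether the two grade distributions differ in any way. The columns can be put in any order, for instance with 'poor' and 'excellent' exchanged, and the P-value stays the same.

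The clinical question is whether grades tend to be better in one arm. A test that discards the order has less power for such a shift. It can also reach significance for a difference that cannot be read as better or worse. Odom's scale is the only overall grade of surgical result among the listed outcomes, so the choice of test matters for how that result is read.

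**Working it through.** **Inputs.** Sample size calculation gives 10 evaluable and 12 randomised patients per arm; Clinical outcome measures gives four ordered grades; Statistical methods gives the 0.05 threshold (two-sided assumed). The article states no power, effect size or grade distribution for Odom's scale, so there is no figure of the plan's own to reproduce.

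**Step 1: which test will be used.** The fallback applies when a cell holds fewer than 5.
- Four grades in use: mean cell count 24/8 = 3 (12 per arm) or 20/8 = 2.5 (10 per arm).
- Three grades in use: 24/6 = 4 or 20/6 = 3.3.
- A mean below 5 means at least one cell is below 5, so Fisher applies.
- Only with two grades in use (24/4 = 6) can chi-square survive. The table is then 2×2 and order plays no part.

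**Step 2: a consistent shift that is missed.** Counts run from poor to excellent, 12 per arm: A = 3/5/2/2, B = 0/2/5/5.
- Column totals are 3, 7, 7, 7, so the midranks are 2, 7, 14, 21.
- Rank sum A = 3×2 + 5×7 + 2×14 + 2×21 = 111. Rank sum B = 2×7 + 5×14 + 5×21 = 189. Each has null expectation 150.
- Exact P over all tables with these margins: Mann-Whitney 0.026, Fisher 0.12.

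**Step 3: relabelling.** For 2/5/4/1 versus 0/1/5/6, Fisher gives 0.041 and Mann-Whitney 0.006. Exchange the 'fair' and 'excellent' counts in both arms: Fisher stays at 0.041, Mann-Whitney moves to 0.195.

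**Step 4: a difference without direction.** A = 5/1/1/5, B = 1/5/5/1.
- Column totals are all 6, so the midranks are 3.5, 9.5, 15.5, 21.5.
- Rank sum A = 17.5 + 9.5 + 15.5 + 107.5 = 150. Rank sum B = 3.5 + 47.5 + 77.5 + 21.5 = 150.
- The arms do not differ in location: Mann-Whitney P = 1.00.
- Chi-square: every expected count is 3 and every deviation is 2, so χ² = 8 × 4/3 = 10.67 on 3 df, P = 0.014. Fisher gives 0.012.

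**Step 5: power.** The grade distributions are assumptions. The cumulative odds of each grade or worse in the control arm are divided by an odds ratio (OR). For example, 25% excellent has odds 1/3; OR 4 gives 4/3, i.e. 57%, and OR 8 gives 8/3, i.e. 73%. Power is summed exactly over all possible pairs of grade tables, two-sided 0.05.

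| Control split (poor to excellent) | OR | 10 per arm: Fisher / Mann-Whitney | 12 per arm: Fisher / Mann-Whitney |
|---|---|---|---|
| 15/25/35/25% | 1 | 4.3% / 3.9% | 4.5% / 4.2% |
| | 2 | 7.9% / 10.6% | 9.0% / 12.9% |
| | 4 | 21.5% / 31.2% | 26.2% / 38.7% |
| | 8 | 44.2% / 57.7% | 52.6% / 68.6% |
| 5/10/35/50% | 1 | 3.4% / 3.0% | 3.7% / 3.4% |
| | 1.5 | 4.3% / 4.5% | 5.1% / 5.2% |
| | 2 | 6.3% / 7.5% | 7.9% / 9.0% |
| | 4 | 16.0% / 19.8% | 21.0% / 24.3% |
| | 8 | 29.6% / 34.7% | 39.2% / 42.7% |

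Gains by subtraction, first split: 2.7 and 3.9 points at OR 2, 9.7 and 12.5 at OR 4, 13.5 and 16.0 at OR 8. Second split: from 0.1 (OR 1.5) to 5.1 points (OR 8). The OR 1 rows show that both tests stay below 5%.

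**The case against.** The strongest reply is that little rests on this test. The Discussion concedes that the trial is too small for its secondary outcomes, says relevant clinical differences are not expected, and limits the aim to checking consistency with published results. The Background calls clinical results of the procedures comparable, so large odds ratios are implausible and grades may well be skewed towards good. The power gain then lies at the low end of the table, where neither test is informative. All of this stands and sets the weight of the point. It does not remove it: the Background also states the secondary goal as a comparison with simple discectomy, and the methods section attaches a significance threshold to this outcome.

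A second reply is that a χ² analysis could mean a chi-square test for trend. The text does not say so, and the grouping with dichotomous outcomes and the Fisher fallback point to the ordinary test.

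Two stronger readings are tempting and are not supported. A reader might infer that the planned test produces false positives. It does not: its error rate under no difference is below 5%, and the pattern in step 4 would have to be a real difference in spread, which nothing in the article suggests. A reader might also infer that changing the test would rescue the Odom comparison. At 10 to 12 per arm it would not.

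**Conclusion.** The point holds as a mismatch between a scale the protocol itself calls ordinal and a test that ignores order. The mismatch is fixed in the text and not repaired elsewhere in the article. The consequence is minor: the primary outcome, the sample size and type I error are untouched. The power figures rest on assumed grade splits and proportional odds. The relabelling property and the worked tables need no such assumption.

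**What to change.** In Statistical methods, take Odom's scale out of the chi-square/Fisher sentence and assign it an exact, tie-corrected Mann-Whitney test, reported beside the four-grade table for each arm. A linear-by-linear trend test would serve equally well. Keep chi-square and Fisher for the dichotomous outcomes. A directional effect estimate with an interval is optional. If only two grades occur, the rank test does no harm.

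The cost is one sentence. No patients, visits or data change, and the Mann-Whitney test is already in the plan for other outcomes.

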**Methods:**

24 subjects between 18 and 55 years old, with radicular symptoms due to a herniated disc between C5 and C7, refractory to conservative therapy are randomized to simple discectomy, or CDA. These groups are preceded by a pilot group of three subjects receiving CDA. Fluoroscopic flexion-extension recordings are acquired preoperatively, and at three and 12 months postoperative. At these same time points, patient reported outcomes are collected, and a neurological examination is performed by and independent physician.

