### Sample size calculation

Sample size calculation is based on the presence or absence of fusion at the operated segment, as the primary outcome is expected to be directly correlated to the presence of fusion. Fusion is defined as < 2° range of motion. At an α set at 0.05, the power (β) of 80% to detect a 40% difference in the amount of patients with < 2° range of motion, the necessary number of participants per group is ten. At a projected loss to follow up of 20% the amount of participants needed is twelve in each group. We also include a pilot group of three patients that will all receive CDA, which will precede the randomised groups, to limit the possible influence of a learning curve. The total number of patients that will be included is therefore 27.

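### NDI, VAS and SF36 are tested with no stated use of the pre-operative score, by a test chosen through a normality check: valid, but less precise than ANCOVA if the pre/post correlation exceeds about 0.25

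*Protocol article*

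**What the plan says.** The Statistical methods section of the protocol article gives one rule for all continuous outcomes: "Continuous outcome measures (NDI, VAS, SF36, sROM) will be analysed using an independent samples t-Test, after testing for normality". The fallback is conditional on that check: "If normality is not met, a Mann–Whitney" U test replaces the t-test. On the threshold it says "Statistical significance will be defined as P < 0.05 in the t-Test". It names no covariate, change score or longitudinal model.

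Pre-operative values exist for every one of these outcomes. For sROM, the section Radiological outcome measures says "Radiological outcome measures are evaluated pre-surgery (0–2 days), and at three and twelve months post-surgery". For the questionnaires, the section Clinical outcome measures places them "At the same three time points at which the radiological analysis takes place". The abstract agrees: "Fluoroscopic flexion-extension recordings are acquired preoperatively, and at three and 12 months postoperative. At these same time points, patient reported outcomes are collected".

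On numbers, the Sample size calculation section says "the necessary number of participants per group is ten", rising to twelve after allowance for 20% loss to follow-up.

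**The concern.** Two features of the rule are open to question.

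- **Baseline.** In a trial this small, the arms will differ noticeably before surgery by chance. With 10 per arm, the difference in baseline means has a standard deviation of √(2/10) = 0.45 SD. Part of that imbalance, in proportion to the pre/post correlation, carries into an unadjusted follow-up comparison as noise. Adjusting for the pre-operative score removes it, using data already collected.
- **Choice of test.** A normality test on 10 to 12 values has little ability to recognise skewness. It therefore lets chance decide whether means or ranks are compared, and this can differ between outcomes and visits.

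What is at stake is the width of the intervals and the consistency of reporting for the clinical outcomes. Validity is not in question.

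**Working it through.** **Inputs from the article.** 10 evaluable per arm (12 randomised; 12 × 0.8 = 9.6); 1:1 allocation; significance at 0.05, taken as two-sided because sidedness is not stated. The article's own sample size concerns the share of patients fused, so there is no planned figure for a continuous outcome to reproduce. Ten per arm is used here only as an input.

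**Assumptions, not in the article.** True difference d = 1 SD; pre/post correlation ρ from 0 to 0.7; normality test taken to be Shapiro–Wilk at 5%.

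**Formulas** (outcome SD = 1, n per arm):

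- t-test on follow-up scores: variance factor v = 1, df = 2n − 2
- t-test on change scores: v = 2(1 − ρ), df = 2n − 2
- ANCOVA: v = (1 − ρ²)(1 + 1/(2n − 4)), df = 2n − 3
- noncentrality = d/√(2v/n); power from the noncentral t
- approximate 95% CI half-width = t(0.975, df) × √(2v/n)

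**Planned test, n = 10.** Noncentrality 1/√0.2 = 2.236, df 18, critical value 2.101: power 56.2%, half-width 2.101 × 0.447 = 0.94 SD, whatever the value of ρ.

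**Alternatives, n = 10** (ANCOVA: df 17, critical value 2.110):

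| ρ | ANCOVA v | noncentrality | ANCOVA power | ANCOVA half-width | change-score power |
|---|---|---|---|---|---|
| 0 | 1.0625 | 2.169 | 53.4% | 0.97 SD | 32.2% |
| 0.2 | 1.020 | 2.214 | 55.1% | 0.95 SD | 38.7% |
| 0.3 | 0.967 | 2.274 | 57.3% | 0.93 SD | 43.2% |
| 0.5 | 0.797 | 2.505 | 65.6% | 0.84 SD | 56.2% |
| 0.7 | 0.542 | 3.038 | 81.7% | 0.69 SD | 77.9% |

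Simulation of the full two-stage rule agrees: about 56%, against 58%, 65% and 82% for ANCOVA at ρ = 0.3, 0.5 and 0.7. With all 12 per arm, the planned test has 64.9% and ANCOVA 62.6%, 64.3%, 66.6%, 74.9% and 89.1% down the same rows.

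**Break-even.** Setting v = 1 at n = 10: 1 − ρ² = 1/1.0625, so ρ = 0.24. At n = 12, 1 − ρ² = 1/1.05, so ρ = 0.22. The lost degree of freedom moves this to about 0.25 at n = 10.

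**Normality check.** At n = 10, Shapiro–Wilk flags exponential data in 44% of samples, gamma (shape 2) in 23% and gamma (shape 4) in 14%. At n = 12, the exponential and shape-4 figures are 53% and 16%. If each arm is tested, truly normal data still switch the method in 1 − 0.95² = 9.75% of comparisons. Type I error of the two-stage rule with exponential data was 5.0% at n = 10 and 5.3% at n = 12.

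**sROM.** Assumed: fused segments uniform on 0–2°; unfused segments mean 8°, SD 4°, held at or above 2°; 10 per arm. With 0% versus 80% fused, the planned rule has about 93% power and ANCOVA 88 to 92% over ρ = 0.3 to 0.7. With 20% versus 60% or 40% versus 80% fused, the two are about equal, near one third. The ordering is sensitive to how the floor at 2° is modelled, so this shows only that a gain from ANCOVA cannot be presumed for sROM.

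**The case against.** The strongest reply is that these outcomes are not meant to carry inference. The Discussion concedes that the sample is too small for the secondary outcomes, expects no clinically relevant difference, and aims only to see whether results fit the literature. A 1 SD effect is then generous. At 0.3 SD and 10 per arm, power is 9.7% as planned and 9.9%, 10.9% and 13.8% with ANCOVA at ρ = 0.3, 0.5 and 0.7, so neither analysis would detect it. This stands and keeps the point minor. It does not remove it: the article still fixes a between-group significance test, and a narrower interval helps a descriptive comparison too.

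A reader might infer more than the documents support:

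- *The planned test is biased or invalid.* It is not. Under randomisation, chance imbalance is already reflected in its standard error, and type I error stays near 5%. The normality check is uninformative here, and the power loss comes from omitting baseline.
- *Baseline is definitely ignored.* The text does not say whether follow-up or change scores are compared. Change scores would use baseline, but they are less efficient than ANCOVA at every correlation tried and no better than follow-up scores at 0.5 or below.
- *Adjustment is free and helps every continuous outcome.* It costs a degree of freedom, loses a little power at low correlation, and has no presumed benefit for sROM, where fusion puts values at a floor.

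**Conclusion.** The point holds as a minor efficiency matter for NDI, VAS-arm, VAS-neck and SF36. The article names the test outright, so this is a choice it fixes and not a detail left to an analysis plan. At 10 per arm and an assumed 1 SD difference, the gain from ANCOVA is about 1 point of power at ρ = 0.3, 9 at 0.5 and 25 at 0.7 (57.3, 65.6 and 81.7 minus 56.2). At ρ = 0.2 it is 1 point worse, and at zero correlation 2 to 3 points worse. The approximate interval half-width moves from 0.94 SD to 0.93, 0.84 and 0.69 SD at ρ = 0.3, 0.5 and 0.7. All of this depends on a correlation that the article does not give. For sROM the point is narrower: the method should not be selected by a normality test. The primary outcome, a dichotomous classification of the segmental motion sequence, is unaffected.

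**What to change.** For NDI, VAS-arm, VAS-neck and each SF36 scale, replace the t-test/Mann–Whitney rule with a pre-specified ANCOVA: treatment plus the pre-operative score, reporting the adjusted difference with its 95% confidence interval at each postoperative visit. Remove the normality test as the selector of the method, and keep one rank-based or permutation analysis as the sensitivity check.

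For sROM, name one method in advance, for example Mann–Whitney, and use it whatever the normality check would show.

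The cost is a change of wording. No new data, visits or patients are needed. The statistical price is one degree of freedom, and 2 to 3 points of power at 10 per arm if the pre-operative score turns out to be uncorrelated with the outcome.
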